#### Screening and enrolment

Participants who met the eligibility criteria and did not fulfil any exclusion criteria during pre-screening were invited to attend an in-person screening visit. At the screening visit, participants received detailed information about the study’s purpose, procedures, risks, and requirements and provided written informed consent. Recruitment commenced in July 2025 and finished in December 2025. The final participant completed the last study visit on 23 February 2026. The study is currently in the biomarker measurement and analyses phase.

Participants were assessed at baseline, during which they underwent evaluations of muscle mass and function, cognitive function, immune function, biological markers, anthropometric measurements, and clinical and digital measurements. Follow-up assessments were conducted at the mid-intervention (week 4) and at the end-of-intervention (week 8), as shown in Table 2.

**Table 2 Tab2:** Overview of assessments performed at each study visit

Measurement	Pre-screening	Screening	Baseline	Week 4	Week 8
**Informed consent**	•	•			
**Lifestyle and medical questionnaire**	•				
**Cognitive function**					
National Institutes of Health Toolbox		•		•	•
**Muscle function**					
Peak oxygen uptake (VO_2_peak)		•		•	•
One-repetition maximum (1RM) test			•	•	•
**Muscle mass**					
Ultrasound			•	•	•
**Immune function**					
CD4/CD8 T cell ratio			•	•	•
Neutrophil-to-lymphocyte ratio			•	•	•
4-plex cytokine			•	•	•
Antigen-specific memory T cell response			•	•	•
Immunosenescence			•	•	•
**Biochemical blood tests**			•	•	•
**Biological analysis**					
DNA methylation profiling			•	•	•
Proteins profile			•	•	•
Metabolite profile			•	•	•
Gut microbiome			•	•	•
**Anthropometry**			•	•	•
**Body composition**					
Bioelectrical impedance analysis			•	•	•
**Cardiovascular outcomes**					
Blood pressure			•	•	•
Carotid-femoral pulse wave velocity			•	•	•
**Handgrip strength**			•	•	•
**Skin advanced glycation end products**			•	•	•
**Lifestyle monitoring**					
OURA ring			•	•	•
**Questionnaires**					
Socio-demographic survey		•			
Wellness questionnaire			•	•	•
Depression Anxiety Stress Scale-21 items			•	•	•
Three-day food diary			•		•
Quality of life					
EuroQol 5-Dimension 5-Level			•	•	•
Short Form 36 Health Survey			•	•	•
Reproductive health					
Androgen Deficiency in Aging Males			•	•	•
Brief Sexual Function Inventory			•	•	•
Female Sexual Function Index			•	•	•
Oral health					
Geriatric Oral Health Assessment Index			•	•	•
Centers for Disease Control and Prevention			•	•	•
American Academy of Periodontology			•	•	•
**Qualitative interviews**			•		•

VO_2_peak was assessed using a cardiopulmonary exercise test (CPET) conducted on an electronically braked cycle ergometer, following a standardised warm-up and an incremental ramp protocol until volitional exhaustion [21] supervised by a research assistant and/or an exercise physiologist. Prior to testing, three blood pressure readings and a temperature measurement were taken to ensure that the risk of adverse events during the test is minimal. If a participant’s blood pressure was elevated, a waiting period of 10–15 min was provided before repeating the measurement. If the blood pressure remained high, the participant was asked to reschedule the session to another day. Participants with an elevated temperature were similarly required to reschedule. Additionally, during the screening visit, cognitive function of the participants was assessed using the NIH Toolbox Cognition Battery, specifically the fluid cognition composite score and the corresponding age-corrected fluid percentage score [22].

### Interventions

All enrolled participants received a multimodal intervention comprising of fundamental and augmented interventions for 8 weeks. Fundamental interventions consisted of lifestyle interventions which were provided uniformly to all participants, whereas augmented interventions involving dietary supplements were tailored to each participant’s gerotype based on individual assessments and needs at the baseline and mid-intervention.

#### Fundamental interventions

All participants received sleep and dietary recommendations, online psychology consultation sessions with a trained clinical psychologist, and a supervised multicomponent exercise program with exergaming (dual-task cognitive-physical training). Sleep recommendations were designed to enhance both subjective sleep quality and objective sleep continuity and regularity [23]. Dietary recommendations were based on principles of the Mediterranean diet [6]. A basic informative study-tailored booklet targeting muscle mass, cognition, and immunity improvement through nutrition was provided to each participant during the initial dietary assessment interview. Dietary habits were evaluated using a nutrition assessment questionnaire conducted in person to allow a more in-depth examination, including whether participants live alone or with others, whether they usually consume home-prepared meals or dine outside, whether they do their own grocery shopping, and to capture the duration of the fasting window between the last meal of the day and the first meal on the following one. A 3-day food diary was also provided to the participants at the beginning and end of the study, with explanations on how to complete it. In addition to these interventions, a trained clinical psychologist conducted two online psychology consultation sessions with each participant to identify psychological facilitators and barriers to enhancing healthy behaviours and promoting adherence to the prescribed interventions during the interim study visits, based on behaviour change models such as COM-B [24]. These sessions also included brief cognitive-behavioural strategies and motivational interviewing.

Supervised multicomponent exercise training was conducted three times per week, with each session lasting approximately 60 min. Each session includes a warm-up, resistance training, and endurance training and concludes with dual-task cognitive–physical training. Resistance training included two sets of 8–15 repetitions across five exercises (plate-loaded seated leg extension, pin-loaded seated row, pin-loaded latissimus pulldown, barbell bench press, and dumbbell lateral raise) performed on resistance exercise machines, with a 2-min rest interval between sets. Training loads were progressively adjusted throughout the intervention to maintain the repetition range while ensuring continued overload. Endurance training was performed on a stationary bike starting at Zone 2 intensity (heart rate reserve 50–60%) and progressing to Zone 3 intensity (heart rate reserve 60–70%). Heart rate was continuously monitored using a Polar arm-band heart rate monitor (Polar Electro Oy, Kempele, Finland). At the end of the session, dual-task cognitive-physical training was performed using digital tools, including exergames and applications such as NeuroTrackerX (CogniSens Athletics Inc., Canada), SportReact reaction lights (SportReact, Croatia), SwitchedOn (SwitchedOn LLC, USA), and ClockYourself (Clock Yourself Pty Ltd., Australia). Training focused on memory and balance in the first session of each week, processing speed and motor skills in the second session of each week, and executive function and mobility in the third session of each week. Sessions were periodised and programmed to be progressively increased both in terms of physical and cognitive load.

Participants received whey protein supplementation (GOLD STANDARD 100% ISOLATE Chocolate Bliss, Optimum Nutrition, Illinois, USA) using the standard 30 g scoop as supplied by the company (each delivering ~ 25 g of protein). The dosage is adjusted according to the body weight categories as follows: 40–59 kg: 1 scoop/day, 60–89 kg: 1.5 scoops/day, and 90 kg and above: 2 scoops/day [25]. In addition, participants took micronized monohydrate creatine supplementation (1.25 g per capsule Optimum Nutrition, Illinois, USA) according to the body weight categories (40–59 kg: 4 capsules/day, 60–89 kg: 6 capsules/day, 90 kg and above: 8 capsules/day) [26] and fucoidan (2.4 g/day, SIRT6Activator®, DoNotAge.org, USA) [27].

#### Augmented intervention

This intervention was given based on participant’s assessment outcomes. At baseline, participants with (1) lower levels of muscle mass (below the 50th percentile for age and sex normative data as provided by InBody 770 analyzer (InBody Co., Ltd., Seoul, South Korea) received urolithin A (500 mg/day, Urolithin A Veggie Capsules: StanYouth® Urolithin A, Bonerge, China), (2) lower levels of VO_2_peak (below the 50th percentile for age and sex normative data) [21] received NMN (300 mg/day, AbinoNutra® NMN, Abinopharm, Inc., USA), and (3) cognitive performance below the 50th percentile for their age- and sex-group based on the NIH Toolbox Cognition Fluid Composite score [22] received a sex-specific multivitamin-multimineral supplement (1 tablet of 1.2 g/day, Centrum, USA). At the mid-intervention time point, the primary outcomes were evaluated to determine the individual progress and potentially adjust the intervention protocol. Based on the decision tree presented in Fig. 2, the intervention initiated at baseline was continued (if the improvement threshold or expected direction of changes is achieved) or adjusted (if the improvement threshold or expected direction of changes is not achieved). The augmented intervention was adjusted by (1) increasing the dose of a given supplement and/or (2) including another supplement. Specifically, if the threshold of improvements in muscle mass and VO_2_peak is not attained, the dose of urolithin A and NMN increased to 1000 mg and 600 mg, respectively [14, 28, 29]. If the threshold of changes in cognition was not achieved, ergothioneine (L-Ergothioneine Veggie Capsules: Dr.Ergo® L-ergothioneine, Shanghai EGT Synbio Group, China and Abinopharm, Inc., USA) was administrated (25 mg, 3 times per week) [30]. Lastly, if the expected direction of changes in immune function is not achieved, the dose of fucoidan was increased to 3.6 g/day [27]. The supplementation strategies and rationale are presented in Table 3.

**Fig. 2 Fig2:**
[figure not shown]
Intervention decision flowchart. Abbreviations: MVM, multivitamin-multimineral; NMN, nicotinamide mononucleotide; VO₂peak, peak oxygen uptake

**Table 3 Tab3:** Supplementation strategies and rationale

Supplement	Baseline (visit 1)	Week 4 (visit 2)	Normative data source	Rationale
Whey protein	Dose is based on body weight as 40–59 kg: 1 scoop/day, 60–89 kg: 1.5 scoops/day, ≥ 90 kg: 2 scoops/day (25 g/scoop)	Same strategy as baseline	Not applicable	Whey protein provides additional protein supplement to improve the protein intake in Singapore (~ 0.6 g/kg from daily diet) to reach ~ 1.2 g/kg daily protein intake target [31, 32]. Protein supplement is considered safe and supports maintenance of lean muscle mass and physical function, which are key determinants of healthy ageing [33]
Creatine	Dose is based on body weight as 40–59 kg: 4 capsules/day, 60–89 kg: 6 capsules/day, ≥ 90 kg: 8 capsules/day (1.25 g/capsule)	Same strategy as baseline	Not applicable	Loading dose up to 25 g/day and maintaining dose of 4–5 g/day are considered safe [34]. It supports muscle mass [35], physical performance [36], and may also have neuroprotective effects [37]. The combination with resistance training introduced additive muscle strength benefit [38]
Fucoidan	2.4 g/day	3.6 g/day given if CD4/CD8 T cell ratio is not improved	Not applicable	Fucoidan is safe up to 4.05 g/day for 2 weeks [39]. Fucoidan, a sulphated polysaccharide derived from brown seaweed, exhibits immunomodulatory properties by enhancing innate and adaptive immune responses, including activation of NK cells and modulation of T cell function [40]. Fucoidan is associated with immune response improvement and improved natural killer cell activity [41]
Urolithin A	500 mg/day given if muscle mass is below the 50th percentile for age and sex normative data	1000 mg/day given if muscle mass is below the 50th percentile for age and sex normative data	InBody 770 analyzer internal database (InBody Co., Ltd., Seoul, South Korea)	Urolithin A is safe up to 1000 mg/day for 8 weeks [42]. As a mitophagy activator, urolithin A improves mitochondrial function and cellular health, which is critical for skeletal muscle health and cellular energy metabolism [14]. Urolithin A may improve muscle function via its antioxidative, anti-inflammatory, mitochondrial function, and cell energy-enhancing effects [43]
NMN	300 mg/day given if VO_2_peak (mL/kg/min) is below the 50th percentile for age and sex normative data	600 mg/day given if VO_2_peak (mL/kg/min) improvement is below 0.6 for men or 0.7 for women	Normative values in Chinese adults [21]. The cut-off threshold for dose escalation comes from scaled values based on the 10–20 years younger target in the planned 1-year intervention	NMN is safe up to 900 mg/day for 60 days [28]. NMN is a precursor of NAD⁺, a key cofactor in cellular metabolism [11]. Increasing NAD⁺ levels enhances mitochondrial function, energy metabolism, and physical performance, including improvements in aerobic capacity (as measured by VO₂peak) [44]
Multivitamin-multimineral	1 tablet given if cognitive performance score is below the 50th percentile for age and sex normative data based on the NIH Toolbox Cognition Fluid Composite score [45]	Continue dose as baseline	NIH Toolbox Cognition Battery database	Multivitamin-multimineral supplementation is widely used globally and helps correct subclinical micronutrient deficiencies that may impair cognitive function and immune health [45]. Adequate micronutrient status is essential for neuronal function, neurotransmitter synthesis, and immune regulation [15]
Ergothioneine	Not prescribed	25 mg (3 times per week) given if cognitive performance score improvement is below 1.3 for men or 1.0 for women [30]	NIH Toolbox Cognition Battery database	Three times 25 mg per week ergothioneine supplement was safe and induced significant improvement in previous clinical trial [30], and its combination with exercise also showed additive benefit on cognition [13]

*ATP*, adenosine triphosphate; *NAD*, nicotinamide adenine dinucleotide; *NIH*, National Institutes of Health; *NMN*, nicotinamide mononucleotide; *VO*_*2*_*pe**ak*, peak oxygen uptake

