### Participant recruitment

#### Pre-screening

Participants were recruited through different social media channels and community engagement events hosted by the NUS Academy for Healthy Longevity. Adults aged 50 to 80 years who had not engaged in regular structured exercise during the past 12 months were considered potentially eligible. Those who expressed interest were directed to the study website to complete a digital pre-screening questionnaire assessing demographics, lifestyle, and medical history after providing written informed consent for pre-screening data collection (Table 1).

**Table 1 Tab1:** Criteria for recruitment

Criteria	Description
Pre-screening inclusion	Aged 50–80 years (both male and female)
	Relatively healthy (have maximum two stable chronic conditions)
	Not engaged in regular resistance or aerobic training in the past 12 months (i.e. untrained)
Inclusion	VO_2_peak below the 75th percentile for age- and sex-specific normative values
	Cognitive performance below the 75th percentile on the NIH Toolbox Cognitive Battery
	Willing and able to comply with exercise and supplementation protocols
	English-literate (can read and understand English)
	Provides written informed consent
	Deemed to have mental capacity, as assessed by the principal investigator
	Able to attend all research visits at MD11, Yong Loo Lin School of Medicine, NUS: screening (~ 2 h), 3 study visits (~ 4–5 h each, 4 weeks apart), 2 interim online visits (~ 45 min), 2 ethics interviews (~ 30 min each), and 3 supervised exercise sessions per week (45 min each)
Exclusion	Significant change in medication in the past 3 months
	History of a major cardiovascular disease (e.g. coronary artery disease, heart failure, and stroke)
	More than two stable chronic conditions (e.g. hypertension, hyperlipidaemia, hyperglycaemia, osteopenia/osteoporosis, osteoarthritis, chronic obstructive pulmonary disease, and type 2 diabetes)
	Known allergies to soy, shellfish/seaweed, mushrooms, or supplement ingredients
	Participation in another interventional clinical trial
	Current use of any study-related supplement unless willing to stop
	Any condition deemed by the principal investigator to jeopardise the safety or study compliance
	Pregnant or planning pregnancy during the study period

*NIH*, National Institutes of Health; *NUS*, National University of Singapore

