### Primary outcomes

The primary outcomes include the feasibility of the study and longitudinal changes from baseline to mid- and end-of-intervention, assessed in muscle function (VO_2_peak and one-repetition maximum strength), muscle mass using ultrasound imaging, cognitive function using the NIH Toolbox Fluid Composite score, and immune function using the CD4/CD8 T cell ratio as indicated in the XPRIZE guideline (version 2.0) [20].

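### The week-4 urolithin A rule is stated in two incompatible ways: missed improvement in muscle mass in the text, position below the 50th percentile in Table 3

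*Protocol article*

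**What the plan says.** **Text (Augmented intervention).** The week-4 review rests on outcomes: "At the mid-intervention time point, the primary outcomes were evaluated to determine the individual progress". The baseline intervention is "continued (if the improvement threshold or expected direction of changes is achieved"), and is adjusted otherwise. For urolithin A and NMN the dose changes "if the threshold of improvements in muscle mass and VO_2_peak is not attained". The section refers to the decision tree in Fig. 2.

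**Instrument.** Under Primary outcomes, the measure is "muscle mass using ultrasound imaging". Bioelectrical impedance on the InBody 770 is described under the secondary outcomes (Body composition analysis). The same device supplies the percentile used to allocate urolithin A at baseline.

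**Table 3.** The week-4 entry for urolithin A reads "1000 mg/day given if muscle mass is below the 50th percentile for age and sex normative data". The baseline entry uses the same criterion for the starting dose. The normative source given is the InBody 770 internal database.

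**Session length.** Table 1 lists "3 supervised exercise sessions per week (45 min each"); the Fundamental interventions section describes training three times per week, "with each session lasting approximately 60 min".

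**The concern.** The text describes a rule based on change since baseline. Table 3 describes a rule based on where the participant stands at week 4, whatever the change. These are different decision rules, and by the plan's own wording they may also use different instruments.

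The Discussion presents dynamic, personalised adjustment as the novel feature of the study, and the Abstract says that the findings will inform a 12-month randomised trial. A reader who wants to reproduce the urolithin A step cannot tell which rule to apply. Supplement adherence is also defined as the amount consumed over the amount prescribed, and after week 4 the amount prescribed depends on the rule in force. If Table 3 is what was done, the step did not respond to individual change.

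**Working it through.** The plan states no figure on this point that could be reproduced. The sample size of 20 is pragmatic and does not enter. The check is a comparison of the two statements, followed by an illustration of how far apart the rules can be.

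**1. The two rules side by side**

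| | Text | Table 3 |
|---|---|---|
| Trigger | improvement threshold missed | below the 50th percentile |
| Type | change from baseline | status at week 4 |
| Measure | primary outcomes, hence ultrasound | InBody 770 norms |
| Threshold | not in the readable text; may be in Fig. 2 | 50th percentile |

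**2. Who is treated differently**

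- *Meets the improvement threshold, still below the 50th percentile:* the text continues the baseline dose; Table 3 changes it.
- *Crosses the 50th percentile with a gain smaller than the threshold:* the text changes the dose; Table 3 does not.
- *Below the 50th percentile only at week 4:* Table 3 read literally gives the week-4 dose. The text speaks of raising the dose of a supplement already given or adding another, so this case is unclear.

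**3. Is this a general shorthand in Table 3?** No. Its other week-4 escalation or add-on rules are change-based and match the text: fucoidan if the CD4/CD8 ratio has not improved; NMN if VO2peak improves by less than 0.6 (men) or 0.7 (women) mL/kg/min; ergothioneine if the cognitive score improves by less than 1.3 (men) or 1.0 (women). Urolithin A is the only exception.

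**4. How often the rules could disagree (illustration only)**

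Every input here is an assumption; none comes from the documents.

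- Baseline position *b*, in SD units of the norm: standard normal, restricted to *b* < 0.
- Week-4 change *d*: normal and independent of *b*. Four mean/SD pairs were used: 0.05/0.1, 0.1/0.1, 0.1/0.2 and 0.2/0.2.
- Improvement threshold *T*: 0, 0.05, 0.1 or 0.2 SD.
- One instrument for both rules, so the mismatch between ultrasound and InBody is left out.

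The text rule changes the dose if *d* < *T*; the Table 3 rule does so if *b* + *d* < 0. The extremes over the 16 combinations are:

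| Mean / SD of *d* | *T* | Text rule | Table 3 rule | Table 3 only | Text only | Disagree |
|---|---|---|---|---|---|---|
| 0.1 / 0.1 | 0 | 16% | 91% | 76% | 0% | 76% |
| 0.05 / 0.1 | 0.2 | 93% | 94% | 5% | 4% | 10% |

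Rows are rounded separately. In the first row P(*d* < 0) = Φ(−1) = 0.159, and with *T* = 0 nobody is changed by the text rule alone, so disagreement is 0.914 − 0.159 = 0.755. In most combinations the disagreement is almost entirely people who met the threshold but stayed below the 50th percentile. When *T* is large relative to the typical change, as in the second row, it is split between the two directions.

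**5. Session length.** 3 sessions × 8 weeks = 24 sessions. At 45 min this is 24 × 45 / 60 = 18 h; at 60 min it is 24 h. The difference is 6 h, one third of the lower figure.

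**The case against.** **Fig. 2 may resolve it.** The text applies its threshold through a flowchart that this review could not see. If Fig. 2 defines the muscle-mass threshold as reaching the 50th percentile, the two triggers largely coincide for those treated at baseline. This stands to the extent that the absence of a numeric threshold cannot be held against the plan. But the text speaks of improvement and does not define it as reaching a percentile. That reading would also leave the instrument open.

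**The instrument conflict rests on one general phrase.** The text itself names the InBody 770 for baseline allocation, and allocating on one device while measuring the outcome on another is not an error. That is fair. What remains is that the text says the primary outcomes decide at week 4, and the primary muscle-mass measure is ultrasound.

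**No planned estimate depends on it.** The statistical section analyses change from baseline in all participants, descriptively. It plans no responder endpoint and no analysis by dose. This stands: the point concerns the description of the intervention and the exposure, not a biased test.

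**A reader might infer that the whole delivered intervention is undefined.** The documents do not support that. The other week-4 rules agree between text and table, the whey, creatine and multivitamin rules are fixed, and supplements dispensed and returned were counted at study visits, so what was supplied should be on record.

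**A reader might also take the share who stay below the 50th percentile as the share affected.** It is not. Many of those people would have their dose changed under both rules.

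**On session length,** the 45 minutes stands in an eligibility line about ability to attend, while the 60 minutes includes warm-up and dual-task training. Adherence is counted in sessions, and both places give three per week. A one-third difference in exercise dose is therefore not shown; only the stated durations conflict.

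**Conclusion.** The contradiction is real and limited to one supplement. As written, the week-4 urolithin A step has two triggers that give opposite instructions to a participant who meets the improvement threshold but remains below the 50th percentile, and the measure that decides is also in doubt. This follows from the wording alone and needs no assumption.

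The frequency does rest on assumptions. The range of about 10% to 76% of those starting below the 50th percentile shows only that the rules are not interchangeable; it does not estimate what happened in this trial. The actual number depends on the improvement threshold and on the participants' data.

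It is worth correcting because it affects the feature that the article presents as new and intends to carry forward. The session-length discrepancy is separate and minor. No view is taken on which rule, dose or duration is right.

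**What to change.** 1. Reconcile the Augmented intervention text, Table 3 and Fig. 2, so that one week-4 criterion for urolithin A is stated, including whether it can apply to someone not given the supplement at baseline.
2. State which criterion and which instrument were actually applied at week 4.
3. Report from existing records how many participants had their urolithin A dose changed, with each one's week-4 percentile and change in muscle mass.
4. If the percentile rule was applied, do not describe this step as adjusted on individual response.
5. As a minor correction, reconcile the session length in Table 1 with the Fundamental interventions section.

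The cost is a text correction and a small table covering at most 20 participants; the last study visit has taken place, so no new data are needed. The downside is that the response-adaptive claim may have to be narrowed for one supplement.
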